### Intervention

The visit schedule is set for weeks 0, 6, 12, 24, and 48. Visits at weeks 0, 6,12, and 24 will be conducted offline, with patients attending the hospital to have relevant information collected by the responsible physician. The visit at week 48 will be conducted online (via phone calls or WeChat).

Conventional treatment: Both groups receive ULT, which in this study is stipulated as febuxostat 40 mg once daily.

TCM Treatment: The intervention group receives QTF granules, while the control group is administered placebo granules, with treatment lasting for 12 weeks. QTF granules constitute a Chinese herbal compound, and the composition of the granules is detailed in Table 2. The placebo granules utilized in this study contain 10% of the same components found in QTF granules. All QTF granules and placebo granules are manufactured and packaged by Jiangyin Tianjiang Pharmaceutical Co., Ltd., located in Jiangsu Province, China. There are no discernible differences in appearance, color, odor, or weight between the QTF granules and placebo granules. The quality of these granules underwent inspection by authorized agencies before declaration, ensuring compliance with specified quality standards. Each dose of QTF granules or placebo granules consists of 9.8g per sachet, to be taken twice daily with 200 ml of warm water, continuously for 5 days followed by a 2-day rest period.

**Table 2 pone.0327864.t002:** Components of Qu-zhuo Tong-bi formula granules.

Chinese name	Latin name	Parts of the substances	Amount (g)
Tu Fu Ling	*Smilacis Glabrae Rhizoma*	Root and rhizome	60
Bi Xie	*Dioscoreae Hypoglaucae Rhizoma*	Root and rhizome	30
Yu Mi Xu	*Stigma Maydis*	Style and stigma	15
Chao Yi Yi Ren	*Coicis Semen*	Mature seed	30
Xi Xian Cao	*Siegesbeckiae Herba*	Aboveground parts	18
Jiang Huang	*Wenyujin Rhizoma Concisum*	Root and rhizome	12
Sang Ji Sheng	*Taxilli Herba*	stem or branches with leaves	15
Yan Hu Suo	*Corydalis Rhizoma*	Root tuber	18
Fo Shou	*Citri sarcodactylis Fructus*	Mature fruit	12

During the treatment period, in the event of gout flares, patients are advised to rest in bed with the affected limb elevated. Within 24 hours, they are required to contact the research personnel for a Visual Analog Scale (VAS) pain assessment: mild (VAS score < 5), moderate (5 < VAS score < 8), severe (VAS score > 8). Early administration of an adequate dose of NSAIDs is recommended within 24 hours. In this study, it is specified as a once-daily administration of 120 mg of etoricoxib (with an onset of action within 1 hour and a half-life of approximately 22 hours), with dosage reduction upon relief of symptoms. Blood and urine samples are collected from patients who consent for further research purposes. In the case of AEs, the use of QTF granules or placebo granules is temporarily suspended until the condition stabilizes.

The observing physician will meticulously record the quantity of medication received, used, and returned by the participants to assess medication adherence and ensure timely documentation in the case report forms. Based on the participant’s adherence, a decision will be made regarding their continued participation in the trial. The exclusion criteria for poor adherence are medication adherence rate = (actual medication amount/ theoretical medication amount) < 80% or > 120%. The medication administrator is responsible for locking the cabinet, sealing the medications, and storing them at room temperature. If a participant withdraws from the study early, any remaining medication should be collected and returned.

Regulations on Concurrent Treatments: During the trial, the use of various anti-rheumatic drugs, muscle relaxants, and analgesics, including both traditional Chinese and Western medicines such as Shenling Baizhu Powder/ Pills and Pingwei Powder, is generally prohibited. Additionally, physical therapies such as massage and acupuncture are not allowed.

If participants need to continue taking other medications or undergoing other treatments due to concurrent diseases, these must be documented in detail in the concurrent medication log.

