**Method:**

This is a multi-center, randomized, double-blind, placebo, parallel-controlled clinical trial conducted in four hospitals in Zhejiang Province, China. A total of 144 patients, aged 18–80 years, will be randomly allocated to either the intervention group (QTF + febuxostat) or the control group (placebo + febuxostat) for a 12-week treatment period. The primary outcome measure is the frequency of gout flares. Secondary outcome measures include the time from the patient’s enrollment to the first occurrence of gout flare (in days), duration of gout flare (in days), health assessment questionnaire disability index (HAQ-DI), pain level (visual analog scale – VAS), rate of achieving target uric acid levels. Occurrences of adverse events, and results from electrocardiograms and laboratory tests, will be monitored.

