## Introduction

Gout is a common metabolic rheumatic disease, and the incidence of affected individuals is increasing [1]. It is characterized by the deposition of monosodium urate (MSU) crystals in the joints, with elevated serum urate concentration (hyperuricemia) being the primary risk factor. Long-term or lifelong urate-lowering therapy can dissolve MSU crystals and reduce the body’s urate level, ultimately alleviating gout flares, making it a fundamental approach in gout management [2]. The initiation of urate-lowering therapy (ULT) is known to carry a risk of gout flares [3,4]. Studies have shown that within the first 3–6 months of starting ULT, the recurrence rate of gout flares ranges from 15% to 70% in patients with hyperuricemia and gout [5–7], potentially increasing the risk of cardiovascular events [8]. Moreover, gout, being a recurrent chronic ailment, not only causes physical discomfort for patients but also imposes a substantial economic burden [9]. Therefore, reducing gout flares is crucial when initiating ULT.

Currently, clinical practice guidelines recommend medications such as colchicine, non-steroidal anti-inflammatory drugs (NSAIDs), or corticosteroids for the management of gout flares during ULT [10]. However, colchicine is associated with significant gastrointestinal, hepatic, and renal toxicity and may potentially suppress bone marrow, necessitating caution [11–13]. Prolonged use of NSAIDs and corticosteroids can lead to serious complications, including gastrointestinal ulcers, which may impact patient adherence to ULT. Given the potential side effects and limitations of current medication for gout prevention and treatment, there is an urgent need to explore new approaches to reduce gout flares.

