**Fig 1 pone.0327864.g001:**
[figure not shown]
Study procedure. ^a^Observe continuously throughout the study and record when it occurs. ^b^Including the number of acute flares of gouty arthritis, the time span from randomization to the first occurrence of an acute attack, and the duration of recurrent acute gouty arthritis. ^c^Red blood cell count (RBC), white blood cell count (WBC), hemoglobin (HGB), neutrophil percentage (NEU), platelet count (PLT). ^d^Alanine aminotransferase (ALT), aspartate aminotransferase (AST). ^e^Blood urea nitrogen (BUN), creatinine (Cr), serum uric acid (SUA).Qu-zhuo Tong-bi formula(QTF).

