### Inclusion criteria

All participants must meet the following criteria:

Meet the above diagnostic criteria and be in the gout intermission stage;TCM diagnosis indicates syndrome of spleen deficiency with dampness obstruction;Serum urate level ≥7 mg/dL (420μmol/L);Aged between 18 and 80 years (inclusive of boundary values), any gender;Having not received urate-lowering drugs such as allopurinol, benzbromarone, or febuxostat in the past month;Relief of gouty flare symptoms (VAS score = 0) for more than 1 week;Acute gout flare≥2 in the past year;Willing to undergo treatment and sign informed consent.

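### As most naturally read, the flare procedure stops at week 12, while flare counts, dates and durations are recorded to week 48

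*Protocol article*

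**What the plan says.** All references are to the protocol article.

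- **Flare procedure (Intervention).** The paragraph starts "During the treatment period, in the event of gout flares, patients are advised to rest in bed with the affected limb elevated". The next sentence reads "Within 24 hours, they are required to contact the research personnel for a Visual Analog Scale (VAS) pain assessment". On flare medication it says "In this study, it is specified as a once-daily administration of 120 mg of etoricoxib".
- **Length of treatment.** The abstract speaks of "the control group (placebo + febuxostat) for a 12-week treatment period", and the Intervention section gives the granules for 12 weeks.
- **Outcomes (Primary outcomes, Secondary outcomes).** Flare frequency, days to first flare, flare duration in days and change in VAS are each recorded at weeks 6, 12, 24 and 48.
- **Contacts (Intervention).** After week 12 the schedule has a hospital visit at week 24 and a phone or WeChat contact at week 48.
- **Fig 1, footnote a.** "Observe continuously throughout the study and record when it occurs". The figure itself is not shown, so the row that the footnote marks is unknown.
- **Other drugs.** A restriction that begins "During the trial, the use of various anti-rheumatic drugs, muscle relaxants, and analgesics" bars these as a general rule. Under Exit criteria, use of medication outside the protocol is one ground on which the investigator may withdraw a patient.

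**The concern.** The article gives its flare procedure a time limit that does not match its outcome schedule. This is more than detail left to a fuller document, because a scope is stated and it is shorter than the period over which flares count.

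Two of the outcomes are measured in days. Without a prompt-contact rule, a flare soon after week 24 may have to be dated, and its length recalled, at a call nearly 24 weeks later. Pain at that flare may not be scored at all while it is present. The Introduction makes post-treatment follow-up an explicit aim, because the team's earlier studies had none, so the weaker capture falls on the part of the trial meant to fill that gap.

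The rule also ends before, or close to the start of, the end of the risk period that the Introduction describes: "within the first 3–6 months of starting ULT, the recurrence rate of gout flares ranges from 15% to 70" per cent.

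A second mismatch concerns treatment. The restriction on analgesics runs for the whole trial, while etoricoxib is specified only in the paragraph that opens with the treatment period. A patient who treats a flare at week 20 could be judged to have used medication outside the protocol, and so be open to withdrawal because the outcome event occurred.

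**Working it through.** The plan gives no figure of its own on this point. The sample size is not an input.

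**Inputs**
- Treatment period: 12 weeks (abstract; Intervention).
- Last outcome record: week 48 (Outcomes).
- Contacts after week 12: weeks 24 and 48 (Intervention).
- Risk period after starting ULT: 3 to 6 months (Introduction), taken as about 13 to 26 weeks.
- Flare rates at 12 weeks: 63.2% on placebo and 38.5% on QTF, 72 patients per arm, 20% dropout (Sample size).

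**Time outside the rule**
- 48 − 12 = 36 weeks; 36/48 = 75%.
- 36 × 7 = 252 days, with two scheduled contacts.
- Gaps between contacts: 24 − 12 = 12 weeks and 48 − 24 = 24 weeks.
- The Introduction speaks of 48 weeks of follow-up after treatment. Taken literally, that would give 48/(12 + 48) = 80%. The 75% follows the visit schedule.

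**Share of the stated risk period outside the rule**
- At 3 months: (13 − 12)/13 = 1/13, about 8%.
- At 6 months: (26 − 12)/26 = 14/26, about 54%.

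This treats the 3 to 6 months as the relevant risk period for these patients. That presumes they stay on febuxostat after week 12, and the article gives no separate duration for it.

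**Ceiling on patients whose first flare could fall after week 12**

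This assumes that the Sample size rates are proportions with at least one flare by week 12.
- Placebo: 72 × (1 − 0.632) = 26.5.
- QTF: 72 × (1 − 0.385) = 44.3.
- Total: 70.8, or about 71 of 144 with no dropout.
- With 20% dropout before week 12, unrelated to flares: 0.8 × 70.8 = 56.6, or about 57.

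Only those who later flare have a date to misrecord. The article gives no rate for that, so the calculation stops at the ceiling.

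**Text side by side**

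The time limit stands in the bed-rest sentence. The contact sentence continues with a pronoun that refers to the same flaring patients, and nothing gives it a wider scope. No other visible text extends the 24-hour contact, the flare VAS or etoricoxib past week 12. Fig 1 footnote a, even if it marks the flare row, supplies none of the three.

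**The case against.** **The limit governs only one sentence.** The opening phrase belongs to the advice on rest, the contact sentence carries no limit, and the etoricoxib sentence is worded for the study as a whole. This stands in part: the 12-week scope is the most natural reading, not the only one. If the sponsor means 48 weeks, the change merely says so.

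**Footnote a may already require continuous recording of flares.** It may, and that would ease much of the worry about counts and dates. It would still leave no contact deadline, flare VAS or flare drug after week 12.

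**Follow-up capture is operational detail, and closer contact on study drug is an ordinary choice.** Diaries or flare forms may well sit in the full protocol, and their absence here is no fault. The point rests on the scope that the article does state.

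**Stronger readings that a reader might infer, and that the documents do not support:**
- *That 54% of the risk period is missed.* This uses only the 6-month end; at 3 months it is about 8%. Likewise, 75% is a share of calendar time, not of flares.
- *That the VAS outcome fails specifically after week 12.* Entry requires "Relief of gouty flare symptoms (VAS score = 0) for more than 1 week", so a visit-day VAS says little between flares. That is equally true at weeks 6 and 12. Nothing says that the score taken at a flare is the VAS outcome.
- *That later flares may not be treated.* The restriction is worded as a general rule and exit is at the investigator's judgment, so this is a mismatch to clarify, not a ban.
- *That the treatment comparison is biased.* Both arms follow the same rule, and no between-arm bias is shown.

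**Conclusion.** The point holds as a mismatch between the stated scope of the flare procedure and the stated outcome window. On the most natural reading, 36 of 48 weeks fall outside the prompt-contact rule, with gaps of 12 and 24 weeks between contacts. Flare dates, durations and flare pain after week 12 are likely to be less exact than those before it.

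The reach is limited. The 12-week comparison behind the sample size is unaffected. Time to first flare is touched only in patients whose first flare comes after week 12: at most about 71 patients, or 57 with 20% dropout, under the planning rates and the assumption stated with them. The amount of under-recording or misdating cannot be derived from the article, and the point is softer if footnote a marks the flare row. It is a cheap improvement rather than a threat to the main result.

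**What to change.** Make two changes in the Intervention section.

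1. Replace the opening time limit of the flare paragraph so that the 24-hour contact and the flare VAS apply from randomization to week 48. Phone or WeChat suffices.
2. Add a sentence stating that protocol flare treatment is permitted throughout the trial despite the restriction on concurrent drugs, and that its use is not a reason for exit.

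The cost is some extra remote patient contacts in weeks 13 to 48 at the four hospitals, under the limited funding that the Discussion mentions. No visits are added and the sample size does not change.

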### Outcomes

#### Primary outcomes.

The frequency of gout flares will be recorded at weeks 6, 12, 24, and 48.

#### Secondary outcomes.

1. The Time span from patient’s enrollment to the first occurrence of gout flares (in days); 2. Duration of gout flares (in days); 3. Health Assessment Questionnaire Disability Index (HAQ-DI) for quality-of-life assessment; 4. Changes in visual analog scale (VAS). 5. Rate of achieving target uric acid levels (Compliance rate = number of eligible patients/total number of patients under observation x 100%; Standard: Gout treatment achievement is defined as lowering serum uric acid levels to below 360 umol/L through the use of uric acid-lowering medications). Outcomes 1–4 will be recorded at weeks 6, 12, 24, and 48. Outcome 5 will be recorded at weeks 12, 24, and 48.

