#### Safety outcomes.

Patients undergo pre- and post-treatment examinations, including blood routine, urine routine, stool routine, liver and kidney function tests (ALT, AST, BUN, Cr, SUA), and electrocardiography, to assess the safety of the interventions in this study. The blood, urine, and stool specimens collected from the patients after completion of the tests are to be disposed of by medical staff according to regulations.

We employ the Common Terminology Criteria for Adverse Events (CTCAE) version 5.0 from the National Cancer Institute of the United States to document the severity of adverse events, categorized from grades 1–5 [25]. According to the classification system devised by the Drug Adverse Reaction Monitoring Center of the Chinese Ministry of Health, adverse events are classified into five levels: “definitely related, probably related, possibly related, probably unrelated, definitely unrelated.” The first three levels are deemed to be associated with the investigational medication [26]. Any adverse events during treatment will be documented based on severity and their causal assessment outcomes. In the event of serious adverse events during the study, immediate measures must be taken and reported to the research design unit’s project manager and ethics committee, which will determine whether to proceed or terminate the study. All adverse events should be monitored until appropriately resolved or stabilized.

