### Statistical analysis

The statistical analysis for this trial will be conducted based on the Per-Protocol (PP) and Intent-to-Treat (ITT) data, conducted by Jiangsu Famous Medicine Co., Ltd., situated in Nanjing, China. Different analysis methods will be employed depending on the type of data measurement or counting.

For the primary outcome, the number of gout flares in each group will be compared using t-tests or Wilcoxon rank-sum tests, with center effects controlled through covariance analysis. For count data, such as time span to the first occurrence of gout flares, duration of acute gouty arthritis recurrence, pain visual analog scale score, HAQ-DI, and safety analysis indicators (like routine blood tests), the same methods will be applied. Measurement data, including the recurrence rate of acute gouty arthritis and the incidence of adverse events, will be analyzed using chi-square tests or Fisher’s exact tests, with center effects controlled through binary or multinomial logistic regression analysis. All hypothesis tests in this study will be two-sided, with a significance level of 0.05. Differences will be considered statistically significant when p < 0.05. SAS version 9.4 will be used for all statistical analyses.

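### HAQ-DI and safety laboratory values are analysed with center as the only named covariate; adding the baseline value of the same variable would gain precision at little cost

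*Protocol article*

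**What the plan says.** All references are to the protocol article; no SAP is at hand.

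- **Statistical analysis.** The number of flares is to be "compared using t-tests or Wilcoxon rank-sum tests, with center effects controlled through covariance analysis". The section then lists further outcomes and ends with "HAQ-DI, and safety analysis indicators (like routine blood tests), the same methods will be applied". Center is the only covariate named. The section does not say whether the quantity compared is the follow-up value or the change from baseline.
- **Safety outcomes.** "Patients undergo pre- and post-treatment examinations, including blood routine, urine routine, stool routine, liver and kidney function tests". A laboratory baseline therefore exists.
- **Intervention.** "The visit schedule is set for weeks 0, 6, 12, 24, and 48", and the week-0 visit takes place in hospital.
- **Secondary outcomes.** For HAQ-DI, among others: "Outcomes 1–4 will be recorded at weeks 6, 12, 24, and 48". Week 0 is not in this list.
- **Inclusion criteria.** "Acute gout flare≥2 in the past year", so flare history is ascertained at screening at least up to that threshold.

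**The concern.** A covariance model is already planned for these outcomes, but its stated purpose is to handle center. For a continuous variable measured before and after treatment, the patient's own baseline is often a stronger predictor of the follow-up value than center is. Leaving it out keeps between-patient variation in the error term that the model could remove. The confidence intervals for HAQ-DI and the laboratory values are then wider than they need to be. This matters somewhat more in a trial of 72 per arm, whose Discussion itself calls the sample small.

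The timing of HAQ-DI adds a practical point. If no score is taken at week 0, it cannot be recovered once a patient has started treatment.

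**Working it through.** **1. Is there a figure in the plan to reproduce?** None for HAQ-DI or laboratory values: the article gives no mean, SD, correlation or target difference for them. Its only sample-size figure is 61 per arm, for flare rates of 63.2% and 38.5% (power 80%, one-sided alpha 0.025). The unpooled two-proportion formula returns it:

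n = (1.960 + 0.842)² × [0.632 × 0.368 + 0.385 × 0.615] / (0.632 − 0.385)² = 7.849 × 0.4694 / 0.0610 = 60.4, rounded up to 61.

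No baseline covariate enters this calculation, so the present point does not change it.

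**2. Inputs for the precision check.** 72 per arm and 20% dropout (Sample size), giving 72 × 0.8 = 57.6 per arm with follow-up. Two-sided alpha 0.05 (Statistical analysis). Assumed: r from 0.1 to 0.7, and a difference of 0.4 SD for illustration.

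**3. Formulas**, with the follow-up SD set to 1:

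- Variance of the comparison relative to unadjusted follow-up values: 1 − r² with the baseline as covariate; 2(1 − r) with change scores.
- Difference detectable with 80% power: (1.960 + 0.842) × √(2/n) × √(1 − r²). At n = 72 without baseline this is 2.802 × 0.1667 = 0.467 SD.
- Power for 0.4 SD: Φ(0.4 / [√(1 − r²) × √(2/n)] − 1.960).

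**4. Results**

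| r (assumed) | Adjusted variance, 1 − r² | Change-score variance, 2(1 − r) | Detectable difference, 72 per arm (SD) | Power for 0.4 SD, 72 per arm | Power for 0.4 SD, 57.6 per arm |
|---|---|---|---|---|---|
| no baseline term | 1.00 | – | 0.467 | 67% | 57% |
| 0.1 | 0.99 | 1.80 | 0.465 | 67% | 58% |
| 0.3 | 0.91 | 1.40 | 0.445 | 71% | 61% |
| 0.5 | 0.75 | 1.00 | 0.404 | 79% | 70% |
| 0.7 | 0.51 | 0.60 | 0.333 | 92% | 85% |

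**5. Price of the extra term.** With an intercept, treatment, three center terms and the baseline, 144 − 6 = 138 residual degrees of freedom remain. One lost degree of freedom inflates variance by about 1 + 1/138 = 1.007, under 1%. At r = 0.1 the net factor is 0.99 × 1.007 = 0.997, so there is practically no gain and no loss.

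**6. Does it matter whether follow-up values or changes are analysed?** No. In every row the adjusted variance is below both 1 and 2(1 − r). Below r = 0.5 a change score is noisier than the plain follow-up value.

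**7. What the outcome list shows about a HAQ-DI baseline.** The Secondary outcomes section also omits week 0 for the urate target (weeks 12, 24 and 48 only). Yet serum urate must be known at entry, because eligibility requires at least 7 mg/dL, and it is among the pre-treatment tests. A missing week 0 in that list is therefore no evidence that a variable is not measured then.

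**The case against.** The case against has several parts, and much of it stands.

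- **A reader might infer that a HAQ-DI baseline is collected and thrown away, or that none is collected.** The documents support neither. The outcome list is silent on week 0, the Randomization and blinding section mentions baseline assessments without itemising them, and the schedule figure is not available here. Only the laboratory baseline is certain.
- **A reader might infer that the comparison is biased by baseline imbalance.** It is not. Under randomization the unadjusted comparison is unbiased, and its standard error already allows for chance imbalance.
- **The gain could be small.** Patients enter between flares with VAS = 0 for more than a week, so HAQ-DI may cluster low at entry. Against that, the syndrome criteria require at least three of four primary signs, three of which concern the joints. Every patient therefore meets at least two joint signs, and some spread in function is plausible. The documents settle neither the spread nor r.
- **The r-squared rule belongs to the linear covariance model.** It does not carry over to the Wilcoxon option. This stands.
- **Covariate lists are often left to the SAP.** True, and naming center does not strictly exclude other terms. But the article does state a method for these outcomes and says what the covariance analysis is for, so the choice is open to comment.
- **For past-year flares only an eligibility threshold is given.** The article does not say that the number is recorded, so that part can only be conditional.

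**Conclusion.** The point holds as a modest precision improvement. For laboratory values the text is clear: a pre-treatment measurement exists and the stated analysis names only center. For HAQ-DI the same improvement depends on a week-0 score, which the article should confirm.

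The size depends on an r that the documents do not give. Over the assumed range the variance reduction runs from 1% (r = 0.1) to 49% (r = 0.7), under a linear model. It concerns secondary and safety outcomes. The stated sample size is unaffected, and the primary comparison is touched only by the conditional flare-count covariate, for which no gain can be calculated from the documents.

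**What to change.** 1. In the Statistical analysis section, state that each continuous laboratory value is analysed by a covariance model with treatment, center and the pre-treatment value of the same variable. Apply the same model to HAQ-DI where a week-0 score is taken.
2. State whether HAQ-DI is recorded at week 0. If it is not, add it to the hospital visit already held then.
3. If the past-year flare count used for eligibility is recorded as a number, include it as a covariate in the primary flare model.
4. Fix these terms before the data are unblinded.

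Cost: one degree of freedom per model and, at most, one short questionnaire at an existing visit. No extra patients or visits are needed.
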